### Economic evaluation

Although the economic benefits of investing in early intervention for children are well established (
Heckman, 2006), and cost effectiveness has been examined in relation to education and health programmes with broad outcomes (e.g.
Knight *et al.*, 2019;
Ludwig & Phillips, 2008), limited work has been done modelling the immediate or long term economic benefits of speech and language interventions (
Le *et al.*, 2020).

An economic evaluation will compare the costs and effects of the Happy Talk intervention, to usual care. The evaluation will also include a budget impact analysis, which predicts the potential financial impact of the adoption and diffusion of Happy Talk, to inform resource or budget planning. The evaluation builds on a previous economic evaluation of our small-scale effectiveness trial (
Frizelle *et al.*, 2021a). The preliminary economic evaluation included a value of information analysis that suggested there was value in collecting further information. This scaled up, full definitive trial will a) provide updated parameter estimates on costs and effectiveness; b) reduce uncertainties around parameter estimates and c) reduce uncertainty around cost effectiveness estimates.

Following standard Health Information and Quality Authority (HIQA) guidelines on conducting economic evaluations a cost utility analysis will be undertaken. In the baseline analysis the perspective of the service provider will be adopted, thus only direct resources utilised will be included. All resources utilised for the delivery of the intervention and standard care will be identified, measured and valued using micro-costing techniques. Resources utilised will be captured by a dedicated resource utilisation questionnaire.

The evaluation will include a primary, secondary and sensitivity analyses. In our primary cost utility analysis effectiveness will be measured using standardised Health Related Quality of Life (HRQoL) questionnaires pre-, post- and at 12 months follow-up. HRQoL measures enable the calculation of Quality Adjusted Life Years (QALYs) as well as an investigation of the sensitivity of these measures with children. To date the use of child appropriate HRQOL is limited, with many studies employing measures and health state values intended for adults. In addition, no health technology assessment (HTA) agency worldwide provides methods guidance on measuring HRQoL in young people. Given persistent issues with valuing child HRQoL, including expected delayed differences in HRQoL and lack of value sets, clinical measures (The PLS-5 and the Focus-34) will be used to test the robustness of results in our secondary analysis. Lastly, the sensitivity analysis will assesses robustness of the effectiveness measures, uncertainty in input and resulting output parameters.

*Analysis:* Difference in costs and effects between the intervention and standard care will be estimated and an Incremental Cost Effectiveness Ratio (ICER) will be estimated. For the baseline analysis if this ICER is less than the nationally accepted threshold (€45,000/QALY) the intervention could be considered cost effective compared to standard care. Results of the probabilistic sensitivity analysis will be presented on Incremental Cost Effectiveness Planes and Cost Effectiveness Acceptability Curves to investigate uncertainty surrounding the output parameters and cost effectiveness decision. The cost results in the economic evaluation will inform the Budget Impact Analysis which will examine budgetary implications associated with national scaling up the intervention over a 5-year period (as per HIQA guidelines).

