1.Children in the intervention group will have better mean scores ona.Receptive, expressive and total language score on the standardized language measure, the Preschool Language Scales (PLS-5)b.Focus on the Outcomes of Communication under Six (FOCUS)c.Paediatric Quality of Life Inventory (PedsQL) and Parent report for Toddlers and Child Health Utility instrument (CHU9D), we have delayed follow up measures to 1 year post to allow time for programme effects to translate into QoL impact.2.Parents in the intervention group will have higher mean scores on the Maternal Responsive Behaviours Coding Scheme (MRBCS)3.Early childhood education settings in the intervention group will have higher means scores on the Classroom Assessment Scoring System (CLASS)4.The intervention will be cost effective for the health care system (measured against common decision thresholds).

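### The baseline cost-effectiveness criterion (ICER below €45,000/QALY) is valid only when the QALY difference is positive, and the protocol does not limit it to that case

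*Protocol article*

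**What the plan says.** The relevant text is in the Economic evaluation section of the protocol article. "Following standard Health Information and Quality Authority (HIQA) guidelines on conducting economic evaluations a cost utility analysis will be undertaken". On the estimates it says: "Difference in costs and effects between the intervention and standard care will be estimated and an Incremental Cost Effectiveness Ratio (ICER) will be estimated". The baseline criterion follows directly: "if this ICER is less than the nationally accepted threshold (€45,000/QALY) the intervention could be considered cost effective compared to standard care". Uncertainty is dealt with in the next sentence: "Results of the probabilistic sensitivity analysis will be presented on Incremental Cost Effectiveness Planes and Cost Effectiveness Acceptability Curves".

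The article does not mention dominance, the quadrants of the plane or net monetary benefit. It does not say that the threshold comparison is confined to a positive QALY difference.

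Two other statements bear on how large the QALY difference may be. The Economic evaluation section lists problems in valuing child health-related quality of life, "including expected delayed differences in HRQoL and lack of value sets". Hypothesis 1c says that quality-of-life follow-up was moved to 1 year so that programme effects have time to show. Cost effectiveness is itself hypothesis 4, and it is one of the listed research questions.

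**The concern.** A ratio of two differences loses the sign of each. Comparing it with a positive threshold gives the right answer only when the denominator, the QALY difference, is positive. With higher cost and fewer QALYs the ratio is negative and passes automatically, although the programme is dominated. With lower cost and fewer QALYs the ratio is positive, but a small ratio then means too little money saved for the health lost, so the inequality should run the other way.

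The threshold sentence is the only decision criterion that the article states for hypothesis 4, and the cost results also feed a budget impact analysis of national roll-out. A criterion that cannot separate the best result from the worst should be put right before results are known.

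**Working it through.** **Inputs from the protocol article.** The threshold is €45,000/QALY. It is an external figure with no derivation to reproduce. The Planned sample size section gives 72 clusters, an average of 10 participants per cluster and an intraclass correlation of 0.05.

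**Inputs assumed, because the article gives none.** The cost difference is ±€400 per child. The QALY difference lies between −0.02 and +0.02. The standard error of the QALY difference is 0.005, 0.01 or 0.02.

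**Step 1: the criterion in each quadrant.** Let dC be the cost difference and dQ the QALY difference, intervention minus standard care. ICER = dC/dQ, and incremental net monetary benefit INMB = 45,000 × dQ − dC. The programme is worth its cost at the threshold when INMB > 0.

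| Case | dC (€) | dQ | ICER (€/QALY) | ICER < 45,000 | INMB (€) | Agree? |
|---|---|---|---|---|---|---|
| Costlier, more QALYs | +400 | +0.02 | 20,000 | yes | +500 | yes |
| Costlier, more QALYs | +400 | +0.005 | 80,000 | no | −175 | yes |
| Cheaper, more QALYs (dominant) | −400 | +0.01 | −40,000 | yes | +850 | yes |
| Costlier, fewer QALYs (dominated) | +400 | −0.01 | −40,000 | yes | −850 | **no** |
| Cheaper, slightly fewer QALYs | −400 | −0.005 | 80,000 | no | +175 | **no** |
| Cheaper, clearly fewer QALYs | −400 | −0.02 | 20,000 | yes | −500 | **no** |

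The two agree in every row with dQ > 0 and disagree in every row with dQ < 0. The dominant and dominated rows have the same ICER, −€40,000/QALY. The reason is algebraic: INMB > 0 means dC < 45,000 × dQ, and dividing by a negative dQ reverses the inequality.

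**Step 2: how often the QALY estimate could have the wrong sign.** For a normal estimate, P(estimated dQ < 0) = Φ(−true dQ / SE).

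| True dQ | SE 0.005 | SE 0.01 | SE 0.02 |
|---|---|---|---|
| 0 | 50% | 50% | 50% |
| 0.005 | 16% | 31% | 40% |
| 0.010 | 2% | 16% | 31% |

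To relate these standard errors to the design, take 72 clusters in two equal arms with 10 analysed per cluster, or 360 per arm. The design effect is 1 + (10 − 1) × 0.05 = 1.45. Then SE = SD × √(2 × 1.45/360) = SD × 0.0898, so the three columns correspond to QALY standard deviations of about 0.06, 0.11 and 0.22. The intraclass correlation was stated for the sample size calculation and not for utilities, so this mapping is also an assumption. Only the 50% in the first row does not depend on the standard deviation.

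**Step 3: what the literal criterion would do at zero true QALY effect.** Hold dC at +€400. The literal criterion passes if estimated dQ < 0, or if it exceeds 400/45,000 = 0.0089. INMB > 0 passes only in the second case.

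| SE | Literal ICER criterion passes | INMB > 0 |
|---|---|---|
| 0.005 | 54% | 4% |
| 0.01 | 69% | 19% |
| 0.02 | 83% | 33% |

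The gap in each row is the 50% of estimates with a negative QALY difference.

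**The case against.** The strongest reply is that the sentence is ordinary shorthand for a costlier, more effective programme, and that its verb is permissive: a result below the threshold could be considered cost effective. A reader might infer that the plan declares success automatically, or that the investigators would call a dominated programme cost effective. The wording supports neither. The cost and effect differences are both to be estimated, so their signs will be known before any ratio is read. On the planned plane, a dominated result falls visibly in its own quadrant.

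A reader might also infer that the plan expects little QALY difference within follow-up. It does not say so. It expects the difference to be delayed, it extended quality-of-life follow-up to 1 year for that reason, and it hypothesises better quality-of-life scores. A near-zero estimate of either sign is possible, but the plan does not predict one. Nor can the plan be faulted for a confidence interval around an unstable ratio, because it proposes none and relies on probabilistic sensitivity analysis.

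Finally, the national guideline that the article follows, or the separate analysis plan, may set a convention for dominance. Neither is shown, so neither can be assumed to correct a criterion that the article itself states.

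These points limit the weight of the concern but do not remove it. The plane and acceptability curves belong to the probabilistic sensitivity analysis, and nothing says that they amend the baseline criterion.

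**Conclusion.** The point holds as a defect in a stated criterion. An ICER below €45,000/QALY indicates cost effectiveness only when the QALY difference is positive, and the article sets no such limit. Taken literally, the criterion admits every costlier, less effective result and points the wrong way for every cheaper, less effective one. That conclusion is algebra and needs no assumption.

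The practical size depends on assumptions. Over the standard errors tried, the chance of a negative QALY estimate is 16% to 40% for a true gain of 0.005 and 2% to 31% for a true gain of 0.010. These figures rest on an assumed QALY standard deviation and on an intraclass correlation that was not stated for utilities. They become wrong decisions only if the sentence is applied without regard to the signs of the two differences. The planned presentations make that less likely, so this is a correction of the criterion and not a challenge to the economic design.

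**What to change.** Preferred: state the baseline criterion as incremental net monetary benefit, 45,000 × QALY difference − cost difference, above 0. Report it with its interval and the probability that it exceeds 0, both read from the probabilistic analysis already planned.

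Alternative: keep the ICER with three additions. Apply the threshold rule only when the QALY difference is positive. Report dominance by name when one option is both cheaper and more effective. Reverse the inequality when both differences are negative.

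If the guideline or the separate analysis plan already contains such a rule, a cross-reference in the sentence would do. Any probability of a wrong-sign QALY estimate quoted in support should be shown over a range and labelled as assumed.

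The cost is rewording and trivial extra analysis. The same cost and QALY data are used.

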## Discussion

The Happy Talk trial aims to mitigate the effects of social disadvantage on child language outcomes and therefore improve the overall life chances of children living in deprivation. The programme is already well established in one region of Ireland and has been shown to be both feasible and acceptable to parents, early years educators and speech and language therapists. The trial is a large scale ‘real world’ effectiveness trial, embedded in the community, which engages with parents and educators, and as such responds to identified evidence gaps. The trial includes an at scale economic evaluation from the perspective of the healthcare provider and outcomes address both functional and standardized measures.

If effective we anticipate the following outcomes:

Evidence that receptive and expressive language difficulties and their functional manifestation can be improved in pre- and early school years, in a cost effective manner, using a public health service delivery model.The availability of a well evaluated speech, language and communication intervention which can be implemented by speech and language therapists in the community,

## Ethics and consent

The study has been reviewed and approved by the Reference Research Ethics committee, Health Services Executive, Dublin and Midlands (with remit for National approval) – RRECB0124PF (14
^th^ March, 2024). Any changes to the protocol will be submitted as an amendment to the original submission. To obtain informed consent, each SLT, educational setting (preschool manager/school principal), educator, parent/ caregiver and child will be provided with an information letter and consent/assent form, adapted to their specific group.

Participation in the study and the identity of the participants will be treated as confidential and no participant identifiable records or results relating to the study will be disclosed to any third party other than the authorized investigators. However, if children are identified as having significant speech and language difficulties that require individual intervention, families will be supported by their interventionist for onward referral.

Personal identifiers will undergo pseudonymization. An encryption key, held securely away from the data, will be accessible to the project PI at site only. In line with the funders (Health Research Board) policy for post-project data publication, consent will be obtained at recruitment for all anonymized data to be shared publicly on an open science repository. Careful evaluation and assessment of publishable data catalogues will be continually reviewed to ensure that data objects will be ‘as open as possible, yet as closed as necessary’ upon completion of the research. The use of data repositories will ensure maximum utility and interoperability of the final data package(s) and assignment of a persistent digital object identifier (DOI). Additional post-study data provenance will be enacted through sharing of analysis scripts and study protocols via the Open Science Framework and/or the HRB Open Research platform projects with accompanying DOI(s). Study findings will be written up as journal publications, and published open access. Findings will also be disseminated to our participants through lay summaries on the project website and will presented to the CHO policy makers at a national meeting. Project co-applicants and collaborators will be eligible for authorship.

## Data Availability

No new data are associated with this article. Extended data: Extended data are available on the Open Science Framework.
*Evaluating a targeted selective speech, language, and communication intervention at scale – the Happy Talk cluster randomised controlled trial* (DOI
10.17605/OSF.IO/NS7U5) (
Frizelle *et al.*, 2024) The project contains the following underlying data. Child Participant Trial and Process Evaluation information leaflet Parent Caregiver Participant Trial and Process Evaluation Consent form Parent Caregiver Participant Trial and Process Evaluation information leaflet Educator Participant Trial and Process Evaluation information leaflet SLT and Educator Participant Trial and Process Evaluation consent form Resource Utilisation Questionnaire Statistical Analysis plan SPIRIT Checklist Trial Governance WHO Trial Registration Dataset Data are available under a CCO license.
